## Abstract

**Background:**

High frequency repetitive transcranial magnetic stimulation (HF-rTMS) has gained interest as a neuromodulation treatment technique for alcohol dependence. Single sessions of HF-rTMS have consistently shown to decrease craving for substances. However, the results of randomized controlled clinical trials investigating the effect of multiple HF-rTMS sessions in alcohol dependence on abstinence rates and craving are inconsistent. Furthermore, they lack information on the effect of HF-rTMS on cognition and brain functioning.

**Methods:**

A single center, single blind, randomized controlled trial with 80 abstinent alcohol dependent subjects in treatment randomized (1:1) to either treatment as usual (TAU) plus ten sessions of active HF-rTMS or TAU plus 10 sessions of placebo/ sham HF-rTMS will be performed. The effects of ten HF-rTMS sessions on craving and neurocognitive functions are obtained. In addition a subset of participants will undergo an MR scanning session before the first and after the last HF-rTMS session in order to investigate the effect of ten HF-rTMS sessions on brain functioning. The primary outcome is the continued abstinence rate after the add-on HF-rTMS treatment.

**Discussion:**

This study uses a randomized controlled trial to examine the clinical, neurocognitive and brain functioning effects of ten add-on HF-rTMS sessions in alcohol dependent individuals in treatment. If the add-on treatment is effective, this may add to the evidence needed for approval of this additional treatment method for alcohol dependence by regulatory authorities.

**Trial registration:**

The Netherlands National Trial Register (NTR), NTR5291, 6-July-2015.

## Background

Substance dependence is characterized by drug seeking and drug use which persists despite negative social and health consequences [1]. In the Netherlands approximately 4–5% of the population is suffering from an alcohol use disorder [2]. In 2014 more than 30.000 individuals were registered at addiction treatment centers in the Netherlands with alcohol as primary substance of abuse [3]. Currently only psychosocial and pharmacological treatments are available for alcohol use disorders. However, these treatments are only moderately effective and more than 50% of all treated patients relapses within one year [4]. In an attempt to improve the treatment of substance dependence, non-invasive neuromodulation has gained attention as a new potential treatment option [5, 6].

High-frequency (HF) repetitive transcranial magnetic stimulation (rTMS) [7] is one of several types of neuromodulation techniques. With this method, a magnetic field penetrates through the skull which can inhibit or activate neurons in the cortex. This magnetic field originates from a coil wherein an alternating electric current is running. The alternating current induces high intensity magnetic pulses that pass the skull and generate an electric current in the neural tissue. By using this technique the activity of the targeted cortical area is manipulated [5, 8]. HF-rTMS became a popular investigational treatment tool for several psychiatric disorders because of its non-invasiveness, tolerability and safety [9].

Individuals suffering from alcohol dependence often experience an intense and abnormal desire for alcohol, also known as craving [10]. Furthermore it is known that alcohol dependent individuals show impaired executive functions, such as diminished cognitive control, cognitive flexibility and working memory [11, 12]. It is believed that perceived craving combined with reduced cognitive control leads to problems in managing craving and consequently relapse [1].

On a neurobiological level craving is associated with heightened striatal activity related to addiction-relevant stimuli, whereas diminished cognitive control is associated with decreased prefrontal activity [13]. One of the areas involved in cognitive control is the dorsolateral prefrontal cortex (DLPFC) [14]. By stimulating the DLPFC with a high-frequency (10 Hz) protocol, the neural activity of this area is enhanced [15] thereby improving cognitive control [16, 17]. Furthermore, it is known that the prefrontal cortex has abundant connections with the striatum [18]. Indeed neuromodulation of the DLPFC has shown to induce changes in neurotransmitter concentrations in the striatum [19] and can decrease feelings of craving with a medium effect size [d = 0.48] (Jansen et al., 2013). The DLPFC therefore seems an excellent target area for treating alcohol dependence because it could enhance cognitive control functions while also influencing striatal functioning and reducing feelings of craving [5]. However, results of clinical trials investigating the effect of *multiple* HF-rTMS sessions on craving are very scarce and inconsistent, with one study stimulating the right DLPFC that reported reduced craving [20] and one study stimulating the left DLPFC that failed finding an effect on craving [21]. Furthermore no studies thus far investigated the effect of multiple HF-rTMS sessions on abstinence rates after a longer period of time.

Altogether the effect of multiple HF-rTMS sessions on abstinence rates, perceived craving and the neurocognitive and neurobiological working mechanisms are poorly investigated (see also, [22]). The current study aims to elucidate the effect of *multiple* sessions of HF-rTMS on abstinence, craving, cognition and brain functioning. We will conduct a single center, single blind, randomized controlled trial with 80 abstinent alcohol dependent subjects in treatment randomized (1:1) to either treatment as usual (TAU) plus 10 sessions of active HF-rTMS or TAU plus 10 sessions of placebo/ sham HF-rTMS. The effect of active versus sham HF-rTMS treatment will be investigated on measures of abstinence, craving, cognition and brain functioning. We expect higher abstinence rates and decreased perceived craving together with improved functioning on the neurocognitive tasks and brain functioning measures in the active HF-rTMS treated group compared with the sham HF-rTMS treated group.

### Aims of the study

This study aims to investigate the efficacy and working mechanisms of 10 add-on HF-rTMS sessions in a treatment-as-usual setup of alcohol dependence.Primary research question:What is the effect of ten sessions of active HF-rTMS on abstinence rates in alcohol dependent individuals in treatment, compared with ten sessions of sham HF-rTMS?Secondary research questions:What is the effect of 10 sessions of active add-on HF-rTMS treatment on total amount of alcohol consumed after treatment in alcohol dependent individuals, compared with 10 sessions of sham HF-rTMS?What is the effect of 10 sessions of active add-on HF-rTMS treatment on days until first relapse after treatment in alcohol dependent individuals, compared with 10 sessions of sham HF-rTMS?What is the effect of 10 sessions of active HF-rTMS on perceived craving levels in alcohol dependent individuals in treatment, compared with 10 sessions of sham HF-rTMS?Additional research questions:What is the effect of 10 sessions of active HF-rTMS on performance on neurocognitive tasks measuring impulsivity, approach avoidance, spatial working memory and compulsivity in alcohol dependent individuals in treatment, compared with 10 sessions of sham HF-rTMS?What is the effect of 10 sessions of active HF-rTMS on brain functioning measures related to cognitive control and craving in alcohol dependent individuals in treatment, compared with 10 sessions of sham HF-rTMS?

## Methods/ design

### Study design

The effectiveness of the HF-rTMS add-on treatment will be tested in a parallel, single center, single blind trial in abstinent alcohol dependent subjects, randomized (1:1) to either treatment as usual (TAU) plus 10 sessions of active HF-rTMS or TAU plus 10 sessions of sham HF-rTMS. A subset of the participants will undergo a magnetic resonance imaging (MRI) scan prior to the first and after the last stimulation session in order to investigate the effects of HF-rTMS on brain functioning (referred to as neuroimaging study part).

### Ethical considerations

This study is approved by the Medical Ethical Committee of the Academic Medical Centre Amsterdam (2015_064) and is registered in The Netherlands Trial Register (NTR) with trial number 5291. Written informed consent is obtained before screening for in and exclusion criteria takes place.

### In- and exclusion criteria

All participants will be recruited when they are three to four weeks abstinent, and are recruited from the Jellinek Addiction Treatment Centre in Amsterdam, The Netherlands. Inclusion criteria are a recent (less than four months after detoxification) DSM-IV diagnosis of alcohol dependence and age between 20 and 65. Exclusion criteria are (1) insufficient knowledge of the Dutch language, (2) Montreal Cognitive Assessment (MOCA) score below 10, (3) current DSM-IV diagnosis of depression, schizophrenia or another psychotic disorder, (4) current recreational drug use, (5) rTMS contraindications (such as a history of epileptic seizures, metal implants near the head, use of imipramine, amitriptyline, doxepine, nortriptyline, maprotiline, chlorpromazine, clozapine, foscarnet, ganciclovir, ritonavir, amphetamines [15]), and if applicable (for the neuroimaging study part) (6) MRI contraindications (such as metal implants or claustrophobia).

### Intervention

The intervention exists of 10 HF-rTMS sessions of the right DLPFC (rDLPFC) on 10 consecutive workdays. The HF-rTMS parameters of the active intervention are 60 10 Hz trains of five seconds at 110% of the motor threshold [23]. The coil will be oriented over the rDLPFC with a horizontal angle of 45° relative to the nasion-inion midline [24]. For the sham stimulation the stimulator will be set at the same settings, but the coil will be tilted 90° relative to the skull [23]. The rDLPFC will be located at position F4 using the International 10–20 EEG system [25]. During the stimulation participants are situated on a comfortable chair with extra neck support. All sessions are applied at the Jellinek addiction treatment centre in Amsterdam. One stimulation session takes approximately 20–30 min.

The motor threshold will be determined at rest before the first and sixth stimulation session, using single pulse TMS in combination with Motor Evoked Potentials. The muscular (left abductor pollicis brevis) response will be measured by visually observing a thumb muscular abduction. Stimulus intensity will be adjusted until there is an abduction in five out of ten trials. For the rTMS sessions we will use a 70 mm double air film coil (Magstim Co., UK) and a Magstim Rapid^2^ stimulator (Magstim Co., UK). The intervention will be applied by an rTMS trained researcher. The training exists of brain stimulation courses, practical rTMS tutorials, hands on training and first aid and emergency response training. During the stimulation session a predefined protocol will be executed.

The HF-rTMS intervention will be added to the treatment as usual (TAU) provided by the Jellinek addiction treatment centre. This treatment consists of an intensive 3–5 days per week program with group sessions of cognitive behavioural therapy (CBT), emotion regulation training, and motivational enhancement therapy. Besides these sessions, every participant has individual sessions with a psychologist and a mentor every week. In the session with the psychologist, comorbidities and other problems of the patients that occur during treatment are discussed. During the mentor session supportive CBT focussing on remaining abstinent is given. Finally, some patients receive pharmacotherapy.

### Procedure and data collection

#### Inclusion procedure

The participants will start their TAU at a clinical or day detoxification unit where they stay for 7–10 days, and continue their treatment during an intensive 3–5 days treatment of at least three weeks. During the beginning of their treatment participants are informed of the study by the researcher. Individuals who are interested in participation are invited for an appointment to provide them with more information. If they are interested, informed consent is signed and the participant is screened for inclusion and exclusion criteria. If a patient meets all inclusion criteria and none of the exclusion criteria he/she will be included in the study by the researcher. After inclusion the patients can indicate whether they also want to participate in the neuroimaging study part. In that case a subsequent MR screening is performed. In order to assure concealed randomization, participants are assigned to the sham or active stimulation group after inclusion, based on the stratification factors anti-craving medication (yes / no) and age (20–40 / 41–65) using variable block sizes (4, 6 and 8) of the randomisation module implemented in the data management system Castor EDC (Castor Electronic Data Capture, Ciwit BV, Amsterdam, The Netherlands, 2016). After randomization participants start with the research procedure described below.

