**Fig. 1 Fig1:**
[figure not shown]
Overview of the measures taken on different test days. Sample characteristics (age, handedness, educational level, medication use, WAIS digit span, NLV, MINI, substance use during life, alcohol use history), neurocognitive tasks (GNGT, AAT, DDT, SWMT, SST, IDED), questionnaires (AUDIT, AASE, BDI, BIS, UPPS, BIS/BAS, STAISTATE, PANAS), extensive craving assessment (AUQ, OCDS, VAS), brief craving assessment (VAS). All these measures will be explained in more detail in the *outcomes and instruments* section. Symbols: X = week before first rTMS session, XX = week after last rTMS session

**Table 1 Tab1:** Overview of measurement instruments and moment of assessment during study. Symbols: X = MR session week before first rTMS session, XX = MR session week after last rTMS session, XXX = three months after last rTMS session, XXXX = six months after last rTMS session, XXXXX = twelve months after last rTMS session

Test day	X	1	2	3	4	5	6	7	8	9	10	XX	XXX	XXXX	XXXXX
WAIS		•													
NLV		•													
MATE-Q		•													
MINI		•													
Alcohol use history		•													
TLFB													•	•	•
VAS		•	•	•	•	•	•	•	•	•	•		•	•	•
AUQ		•				•					•		•	•	•
OCDS		•				•					•		•	•	•
DDT		•				•					•				
Go/No-go		•				•					•				
SST		•				•					•				
AAT		•				•					•				
SWMT		•				•					•				
IDED		•				•					•				
Urine test	•											•			
Cue reactivity	•											•			
Stroop	•											•			
MIDT	•											•			
Resting state	•											•			
ASL	•											•			
AASE		•				•					•		•	•	•
AUDIT		•													•
BDI		•				•					•				
BIS/BAS		•				•					•				
BIS		•				•					•				
UPPS		•				•					•				
STAI/STATE		•				•					•				
PANAS		•				•					•				
Side effects			•	•	•	•	•	•	•	•	•				
Alcohol use study		•	•	•	•	•	•	•	•	•	•				

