##### Neuroimaging study part

The outcome measures concerning brain functioning will be obtained in the week before the first stimulation session (i.e. to measure baseline brain functioning) and in the week after the last stimulation session (i.e. to measure the effect of HF-rTMS). Before the participants enter the scanner they perform a urine alcohol and drug screening and practice the tasks that will be conducted in the MRI scanner.

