##### Additional craving assessment

The effect of HF-rTMS on craving will also be assessed using the short (5-item) version of the Obsessive Compulsive Drinking Scale (OCDS) [35]. This questionnaire will be assessed prior to the first, and after the fifth and tenth stimulation session and at the 3, 6 and 12 months follow-up.

To assess the acute effect of HF-rTMS on craving two 100 mm visual analogue scale (VAS) ranging for 0 (not at all) to 100 (very much) will be assessed prior and after every stimulation session. Participants will be asked to indicate (1) their current desire to consume alcohol: “How much do you feel like drinking alcohol right now?” and (2) their current urge to drink alcohol: “How strong is your urge to drink alcohol right now?” by drawing a line on a VAS scale.

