#### Neurocognitive measures

Despite the role of the prefrontal cortex in higher cognitive processes [44], the effect of HF-rTMS over the rDLPFC on neurocognitive measures in alcohol dependent individuals is poorly investigated (see also [22]). Therefore the effect of active HF-rTMS compared with sham HF-rTMS on several neurocognitive tasks will be assessed before the first, after the fifth and tenth HF-rTMS session. Neurocognitive tasks will focus on cognitive control and other relevant processes such as approach behavior and working memory. Participants will be situated in front of a finger operated touch screen tablet (Hewlett-Packard; Windows 8.1) on which the tasks will be conducted.Go/ No-go Task (GNGT): This task (adapted from [45]) measures the ability to refrain from action initiation [46]. Participants see a number (‘1’, ‘2’, ‘3’, ‘4’, ‘5’, ‘6’, ‘7’, ‘8’, ‘9’) projected on a screen in front of them. They are instructed to press the spacebar with their right hand as soon as they see a number, but not if it is the number ‘3’ (=no-go trial) (Fig. 2a). The outcome measure will be the number of commission errors, i.e. a response to a no-go trial, reflecting action impulsivity. The higher the number of commission errors, the more impulsive an individual is.Approach Avoidance Task (AAT): This task (adapted from [47]) measures the bias towards approaching alcoholic beverages. During this task pictures from a validated dataset [48] of alcoholic beverages, sodas and neutral objects (for example scissors) are presented on a screen in front of the participant. The pictures are rotated 3° towards the left or right, indicating whether a participant has to pull or push a picture using a joystick (Fig. 2b). When a picture is pulled or pushed the size of the picture increases or decreases respectively. The bias score per stimulus category [alcohol/ soda/ neutral] will be calculated by subtracting the median reaction time of the approach (pull) trials from the median reaction time of the avoid (push) trials. When the result of this subtraction is positive, this indicates a relative faster approach compared to avoid, i.e. an approach bias. When the result of the subtraction is negative this indicates a relatively faster avoid compared to approach, i.e. avoid- bias.Delay Discounting Task (DDT): This task (based on [49]) measures the extent of impulsive decision making. Participants are presented with a choice between an immediate (lower) and a delayed (higher) hypothetical monetary reward (Fig. 2c). The value of the immediate reward varies across the trials in one block, and depends on the responses that are made [49]. The outcome measure will be the area under the discounting curve (AUC), reflecting the degree of discounting by delay [50]. Impulsive choice behavior is indicated by a smaller AUC.Spatial Working Memory Task (SWMT): This task is part of the Cambridge Neuropsychological Test Automated Battery (CANTAB) test battery, and measures the ability of a subject to remember spatial information and manipulate this using working memory. During this task participants are presented with a number of colored squares (or boxes for the participant) shown on a screen. The participant is instructed to find a blue token hidden in each box, and use this token to fill up the black empty space on the right side of the screen (Fig. 2d). In order to open a box, and see whether there is a hidden token inside, the participant needs to touch the box on the screen. If no token is found the participant must continue its search until a token is found. When there is a blue token inside, the participant must now touch the black empty space to fill up this space with the token. Now the participant has to begin a new search. The next token will only be hidden in a box that so far has been empty. This procedure is repeated until all tokens are found and the entire empty space is filled with tokens. The task starts with three boxes, and this will increase to four, six and eight boxes. Touching a box where the token had already been found is considered an error. The outcome measure will be the number of errors a subject makes and reflects working memory capacity. The more errors a subject makes, the lower the working memory capacity.Stop Signal Task (SST): This task (part of the CANTAB test battery) measures the ability of an individual to inhibit an ongoing action [46]. Participants are presented with a white ring on a black screen. In the ring a white arrow pointing either to the left or to the right appears. The participant needs to press the left button if the arrow points to the left and the right button when the arrow points to the right as fast as possible (go trial). During some trials the participant hears an auditory signal (beep), after the arrow appears, which indicates they have to stop their response and not press the button (stop trial) (Fig. 2e). The outcome measure will be the amount of successful stops and reflects the capability of stopping an initiated response. The lower the number of successful stops, the more impulsive an individual is.Intra-dimensional/ Extra- dimensional Set Shift (IDED): This task (part from the CANTAB test battery) tests rule acquisition and reversal learning. Two stimuli are presented on a screen from which the participant has to choose one by pressing on the screen. These stimuli are made up of two artificial dimensions: color-filled shapes and/or white lines. The stimuli presented can be either simple (just one of the two dimensions) or compound (stimuli contain both the dimensions). The task contains 9 blocks increasing in difficulty (Fig. 2f). After pressing the stimulus on the screen the computer gives feedback on whether this was the correct stimulus. In this way participants can learn the task rules. After six correct responses (learning criterion) the program changes the rule, and thereby the participant reaches the next block. If the participant does not reach the learning criterion the test terminates after 50 trials. The outcome measures will be the number of trials needed to reach the next stage (indicating the rule learning capacity), and the number of errors made after a rule change (indicating the capacity of reversal learning) [51]. Higher numbers indicate lower rule learning and reversal learning capacity.

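### Randomisation comes before the baseline scan and all day-1 baseline tests in a single-blind trial, and nothing says the arm is withheld until they are done

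*Protocol article*

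**What the plan says.** The Inclusion procedure section of the protocol article gives the order of events. First, "informed consent is signed and the participant is screened for inclusion and exclusion criteria". Next come inclusion and, for those who want it, MR screening. Then "participants are assigned to the sham or active stimulation group after inclusion", stratified by anti-craving medication and age group, with blocks of 4, 6 and 8 in Castor. The section closes with "After randomization participants start with the research procedure described below".

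The procedure that follows holds the baselines:

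- **Scan.** The brain-function measures "will be obtained in the week before the first stimulation session". The legend of Table 1 agrees: "X = MR session week before first rTMS session".
- **Neurocognitive tasks.** These "will be assessed before the first, after the fifth and tenth HF-rTMS session".
- **OCDS.** It is taken "prior to the first, and after the fifth and tenth stimulation session".
- **AUQ and the other questionnaires.** Table 1 puts them on test day 1.

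The Discussion accepts that the trial is single blind because sham requires the coil to be tilted. It argues that double blinding is unnecessary because outcomes are self-reported and the researcher scores nothing. The primary analysis section imputes missing data for randomised participants who had one or more stimulation sessions.

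**The concern.** A baseline is safest when nobody involved can know the arm. Here it is taken after allocation, in a trial where the person who stimulates must know the arm. If that knowledge is present at baseline, the way a task is explained, practised or encouraged could differ between arms. Any model of change from baseline would then carry the difference as if it were a treatment effect.

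The second issue is the interval between allocation and first stimulation. Whoever leaves in that interval counts as randomised but has had no session, so the imputation rule does not cover them. The analysed set then falls short of everyone randomised, which sits uneasily with the stated intention-to-treat principle.

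**Working it through.** The plan gives no figure to reproduce. The check is one of sequence, and then of which analyses depend on the baseline.

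**Step 1: sequence.** The Inclusion procedure section runs: consent, eligibility screening, inclusion, MR screening if wanted, randomisation, research procedure. The baseline scan and test day 1 both belong to the last item. No section places an outcome baseline before randomisation. Only eligibility data and the two stratification factors are necessarily known beforehand.

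**Step 2: knowledge of the arm.** The Intervention section says that a trained researcher stimulates. The Inclusion procedure section says that the researcher informs and includes participants. Neither says whether this is one person, who runs the baseline tests, or when the Castor result is seen. No sentence withholds the allocation until baseline is complete.

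**Step 3: which analyses use the baseline.**

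| Outcome | Time points in the analysis section | Baseline used? |
|---|---|---|
| Abstinent days (primary) | 180 days after last session | No |
| Alcohol consumed, days to relapse | After treatment | No |
| AUQ, OCDS models | Post-treatment, 3 and 6 months | No |
| Six neurocognitive tasks | Baseline, intermediate, post | Yes |
| Questionnaires | Baseline, intermediate, post | Yes |
| Imaging | Baseline scan against scan after treatment | Yes |

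The outcomes section describes the AUQ outcome as a change, but its model lists no baseline time point, so it is counted here as unaffected.

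**Step 4: how a baseline shift would act.** The change contrast is (post_active - base_active) - (post_sham - base_sham). Let researcher influence shift the active-minus-sham difference by d_base at baseline and by d_post after treatment. The error in the contrast is then d_post - d_base. A baseline shift enters in full, with its sign reversed. The documents give no basis for a value of either term.

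**Step 5: how many are involved.**

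- Day-1 baselines after allocation: all of about 80 participants.
- Baseline scans after allocation: 2 x 28 = 56, and 56 / 80 = 70% of the sample.

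**Step 6: losses before session 1.** The documents give neither the interval from allocation to first session nor a loss rate for it. Only the imaging participants have a visit stated to fall in the preceding week. With an assumed loss of 2% to 5%:

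- 56 x 0.02 = 1.12
- 56 x 0.05 = 2.8

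That is about 1 to 3 participants randomised but outside the imputed set.

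**The case against.** The strongest reply is that the bias is conjecture. Participants are blinded, the neurocognitive tasks run on a tablet, the questionnaires are self-report and the rest are scanner measures. The article condenses a fuller protocol, which may say who tests and when the allocation is released. The same influence could act at the day-5 and day-10 tests, where stimulation has begun, and moving randomisation does nothing about that. In the terms above, the fix sets d_base to zero and leaves d_post. Losses before any stimulation, in participants who do not know their arm, are unlikely to depend on arm and would mainly cost precision.

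Most of this stands, and it limits the point. A reader might infer that one researcher does everything and knows the arm at baseline. The documents do not say so. A reader might also infer that the primary result or the craving results are biased. The time points in those analyses rule out this route.

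Two things survive. The order of events is a stated rule, not a gap left by condensation. And the Discussion's defence of single blinding rests on self-report, whereas the tasks most exposed here (Go/No-go, stop-signal, set-shifting, working memory, Stroop) measure performance, which can respond to encouragement even when a computer scores it.

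**Conclusion.** The point holds in a limited form. As written, the baseline scan and all day-1 baselines follow allocation, and nothing in the article keeps the arm from the researcher until they are complete. Knowledge of the arm at baseline is possible, not established.

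The possible bias is of unknown size. It concerns additional outcomes only: the neurocognitive tasks and questionnaires in about 80 participants, and imaging in a planned 56. The primary outcome is touched only through losses before session 1. These come to about 1 to 3 of the 56 imaging participants, which rests wholly on the assumed 2-5%.

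A reader might apply that percentage to all 80 and get 1.6 to 4. The argument for a gap of up to a week comes from the scan, however, and the documents state no such gap for participants without one. Nor do they show that early allocation has no practical purpose; they simply give no reason for it.

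This is an inexpensive improvement worth making, not a threat to the main conclusion.

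**What to change.** Reword the end of the Inclusion procedure section so that the Castor allocation takes place once all baseline measurements are complete (including the baseline MR session where it applies) and directly before the first stimulation session. Keep the strata and block sizes as they are. If scheduling makes this impossible, keep the present order but state that the allocation is withheld from the researcher until that moment.

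Either version closes the route at baseline. Only later randomisation also removes most of the losses between allocation and session 1. Neither addresses possible influence at the day-5 and day-10 tests.

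The cost is some baseline assessments, including a few MR sessions and part of a test day of about 4 hours, in people who are then never randomised. No visits or randomised participants are added.
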